### Biospecimen collection, processing, and storage

Peripheral blood, nasal samples and/or saliva will be collected from index cases and eligible household contact members at each study visit. Refer to Table 2. Samples will be taken by experienced staff, trained in the home visit procedures. All samples will be kept on ice and transported to the laboratory.

Each saliva sample will be collected by passive drool collection and spitting into a sterile container. Saliva samples intended for viral PCR will be collected in phosphate saline buffer (PBS) and kept on ice until final storage in the laboratory. Participants will be asked not to eat, smoke, drink or brush their teeth 30 min prior to the collection. Saliva collection will be followed by collection of nasal fluid samples using a synthetic absorptive device (Nasosorption FX, NSFL-FX-11 or NSFL-FXI-13), that absorbs the mucosal lining fluid. A second nasal sampling will consist of inserting an interdental brush into the nostril and gently twirling the brush against the inferior turbinate which runs along the lateral wall of the nasal passage. After collection, the brush is inserted into a sterile tube pre-filled with RNAlater (Life technologies cat# AM7021) to allow RNA stabilization until analysis. Blood samples are collected last, and a total of 23 ml of peripheral blood will be obtained from an easily accessible vein by experienced staff. A 21G butterfly needle will be used to draw blood into 3 distinct collection tubes; IVD PAXgene blood collection tube (BD, Cat. No. 762165) for RNA samples, CTP Vacutainer (BD, Cat. #362761) for mononuclear cells (PBMC) collection and Lithium Heparin vacutainers (BD, cat# 367526) for the remainder. At the end of collection, all biospecimens will be transported to the laboratory for further processing and/or storage.

Saliva, nasal lining fluid samples and nasal brush collection tube contents will be aliquoted in cryovials and stored at -80 °C. Blood PAXgene tubes will be kept at room temperature for a minimum of 2 h for complete lysis of blood cells and then stored at − 80 °C for subsequent transcriptomic analysis. 200 µl of heparinized blood will be transferred to a cryovial and stored at − 80 °C without any further processing, for subsequent epigenetic analysis. A total of 600 µL of whole blood will be processed as previously described [19] using Smart tube lysis and fixing solutions as per the manufacture’s recommendations and stored in cryovials at − 80 °C for subsequent flow cytometric analysis. Plasma will be separated from the remainder of the blood by centrifugation and aliquote for storage at − 80 °C. All specimen aliquots will be barcoded and sample location as well a specific processing information recorded electronically, to ensure optimal tracking and standardization.

### Treatment assignment and randomization

Households will be randomized as clusters to receive either IFN ß-1a treatment or standard of care, once a household meets all the inclusion and none of the exclusion criteria. Households will be randomized to IFN ß-1a treatment or standard of care at a 1:1 ratio. The minimization technique (biased coin, *p* = 0.7) will be applied to achieve balance between groups stratified by the total number of people within the household. This will be implemented through a platform provided by the Telethon Kids Institute (https://qminim.telethonkids.org.au/).

Households will be randomized during the first home visit, once eligibility is confirmed, participants have signed informed consent, and baseline data collection procedures are completed. Field team members will contact the research laboratory, at which time the household assignment to treatment or standard of care will be made by the randomization software. Participants and study staff will not be blinded to randomization of treatment or standard of care, but all data analyses will be blinded to allocation.

### Intervention arm

Participants (index cases and treatment eligible household contacts) will receive 125 µg of pegylated IFNß-1a (PLEGRIDY®, Biogen) administered on Study Days 1, 6 and 11 (i.e. for a total of 3 doses). IFN ß-1a will be administered at the home of the participant, via subcutaneous injection from appropriately trained trial staff, for whom administration of subcutaneous injections is within their normal scope of practice (e.g. nurse or physician). The staff will remain at the home for 20 min after the last individual in a household receives their dose of IFN ß-1a, before leaving the residence, to ensure no immediate adverse events associated with IFN administration occur. All field team staff will be supplied with appropriate personal protection equipment, trained in the use of this equipment and in protocols for infection control, and will always attend in pairs. Staff administration of IFN ß-1a will ensure medication adherence.

### Control arm

Participants randomized to the control group will receive standard of care, including symptom-based supportive treatment provided by the individual’s personal medical provider. This could include acetaminophen, non-steroidal anti-inflammatory drugs, cough suppressants, antibiotics, inhaled bronchodilators. Participants in this arm will not receive any IFN ß-1a treatment or a placebo. This standard of care approach was selected as the comparator, since no other approved intervention medications are available for non-hospitalized cases.

All participants, regardless of their allocation group, will receive a brochure with the recommendations of the Chilean Government for patients with COVID-19, including household isolation. Within each household, the index case will be asked to isolate from their contacts.

### Data management and confidentiality

Clinical and laboratory data for this trial will be collected and managed using REDCap (Research Electronic Data Capture) electronic data capture tools hosted at the Telethon Kids Institute, Perth, Australia [20, 21]. REDCap is a secure, web-based application designed to support data capture for research studies, providing: (1) an intuitive interface for validated data entry; (2) audit trails for tracking data manipulation and export procedures; (3) automated export procedures for seamless data downloads to common statistical packages; and (4) procedures for importing data from external sources. Data will be stored securely on a Telethon Kids Institute server (restricted access), in accordance with the requirements of good clinical practice and Health Privacy Principles [18]. All paper files will be stored securely at the research lab. Only members of the research team will have access to data, including the final trial dataset. There are no contractual agreements that limit the investigators access to data. The dataset will be available to the public upon request and approval by the investigators.

### Data and safety monitoring

An independent Data and Safety Monitoring Board (DSMB) will be convened and will meet weekly for the first four weeks of the study and then monthly until database lock. The DSMB will monitor data completeness, duplication, rates of enrollment and participation, and the general study conduct. The DSMB will be composed of individuals with the appropriate expertise, including at least three independent clinicians and/or biostatisticians who, collectively, have experience in the management of biostatistics and the conduct and monitoring of randomized controlled trials. Members of the DSMB will be independent of trial conduct. The DSMB will review data from the treatment and control groups of the trial. At each meeting, a descriptive summary of withdrawals, serious adverse events and non-serious adverse events thought to be related to the study drug will be provided, along with outcome data for the primary outcomes. The DSMB will provide its input to the trial chief investigator.

Adverse events (AE) and adverse reactions (non-serious and serious) will be captured from the time of randomization until study day 29. For the purposes of this study, the investigator or delegate is responsible for recording all AE, regardless of their relationship to study treatment, with the following exceptions: (1) conditions that are pre-existing at enrollment and do not deteriorate; (2) abnormal laboratory values unless deemed clinically significant by the investigator and documented as such; (3) the onset of COVID-19 symptoms among asymptomatic household contacts or new symptoms within the household index case. The seriousness of an AE will be assessed by an investigator with the following exceptions: (1) elective surgery planned at the time of enrollment, and (2) hospitalization due to progression of disease will not be considered a serious adverse event (SAE) for the purposes of this trial.

All adverse events/serious adverse events will have their relationship to the trial intervention and severity assessed by the investigator who evaluates the adverse event, based on temporal relationship and his/her clinical judgment. All severe adverse events will be reported immediately to the sponsor, except for those SAEs that are identified as not requiring immediate reporting. The immediate reports should be followed promptly by detailed, written reports. Clinic trial liability insurance will cover costs for participants who suffer harm during trial participation. Investigators will ensure harmed participants receive treatment for their condition.

IFN treatment is known to induce injection site erythema and, in up to 80% of recipients, an ‘influenza like’ syndrome, comprising fever, headache and body aches. Importantly, there are no respiratory signs or symptoms associated with IFN treatment, i.e. the response to IFN treatment is different than COVID-19 disease. However, ‘flu-like symptoms’ also occur in COVID-19 disease, and could lead to an increase in clinical tests in the IFN treated cohort if not appropriately managed. There are several strategies that may mitigate this potential response to IFN treatment that already constitute standard practice for multiple sclerosis (MS) patients on IFN therapy. Participants will be informed about the likely side effects of IFN treatment and asked to monitor and manage these. Monitoring consists of self-assessment of symptoms (there are no respiratory symptoms or anosmia known to be associated with IFN use) and the time frame during which this ‘influenza like’ syndrome following IFN treatment occurs (restricted to the first 4–24 h after administration of an IFN dose). Management consists of advising the participant to take acetaminnophen (provided to the participant) from the time of IFN administration up to 24 h after, to reduce the likelihood of this ‘influenza like’ syndrome. This approach is recommended for individuals with MS receiving IFN therapy (see PLEGRIDY package insert product monograph) and reduces syndrome symptoms by 80%.

Interferon ß-1a is safe when taken during pregnancy, with no evidence of increased rates of congenital anomalies or spontaneous abortions, according to data reported by the European IFNbeta Pregnancy Registry. If a female subject is diagnosed as pregnant by a positive.

pregnancy test or other method of diagnosis, the principal investigator will notify the DSMB and Ethics Committee of this. If the subject is enrolled in the IFN arm and still has outstanding IFN doses to be administered, the decision whether to continue IFN treatment or not will be made by weighing the risk/benefit on a case by case basis.

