Participants in the IFN ß-1a treatment arm will be alerted to potential influenza-like symptoms that are sometimes associated with IFN treatment and will be advised to take the provided acetaminophen (1000 mg 4 times per day) from the time of IFN administration until 24 h post-injection, to reduce the likelihood of these symptoms. Participants in the control arm will also be instructed to take the provided acetaminophen within 24 h of the first home visit, to conform with the intervention group. Participants will receive information on the potential risks of IFN ß-1a treatment during pregnancy and other contraindications for PLEGRIDY® use.

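### The DSMB's routine summary shows non-serious adverse events only if judged drug-related, so in this open-label trial without placebo it gives no between-arm comparison of them

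*Protocol article*

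**What the plan says.** The section on data and safety monitoring fixes the content of the board's report. Whenever the board meets, "a descriptive summary of withdrawals, serious adverse events and non-serious adverse events thought to be related to the study drug will be provided", and it also receives data on the primary outcomes. The sentence shortly before it gives the general intention: "The DSMB will review data from the treatment and control groups of the trial".

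Four other statements bear on how that summary will read.

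- **Control arm:** "Participants in this arm will not receive any IFN ß-1a treatment or a placebo".
- **Treatment assignment and randomization:** "Participants and study staff will not be blinded to randomization of treatment or standard of care".
- **Who judges relatedness (Data and safety monitoring):** the investigator who evaluates the event, "based on temporal relationship and his/her clinical judgment".
- **What is recorded (Data and safety monitoring):** the investigator is responsible for "recording all AE, regardless of their relationship to study treatment", but with three listed exceptions. The third covers COVID-19 symptoms that begin in contacts who had none, and new symptoms in the index case.

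The same section says that interferon produces a flu-like syndrome in up to 80% of recipients and that such symptoms are also part of COVID-19. The section on home visits has participants in both arms keep a symptom diary. The article does not say that diary data go to the board.

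**The concern.** A safety board in a randomised trial learns most from the difference in event rates between arms, because that difference does not require anyone to decide what caused an individual event. A relatedness filter replaces the comparison with a set of individual causal judgements. Where there is a placebo and attribution is blinded, the filter at least applies to both arms alike. Here there is neither.

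Two errors become possible. An effect of interferon that an investigator ascribes to COVID-19 does not reach the board through this summary. A COVID-19 symptom ascribed to interferon reaches it as harm, with no control rate beside it. The first matters more for an unexpected non-serious effect, because an investigator is less likely to call related what nobody anticipated. Safety is a stated secondary objective, and the drug is given to contacts who have no symptoms at entry, so tolerability is part of what the board must weigh.

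**Working it through.** The article states no figure for this point, so there is nothing to reproduce. The check is of the reporting rule, followed by an illustration.

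**1. The control count.** The filter asks whether an event is thought related to the study drug. Controls are not given it and have no placebo. The number of control events that can pass is therefore 0, whatever the true rate. Controls are given one trial-supplied product: "Participants in the control arm will also be instructed to take the provided acetaminophen within 24 h of the first home visit". Table 2 lists acetaminophen as pre-medication, separately from administration of the study drug. Even if an event were attributed to it, that would not yield a control rate of flu-like symptoms.

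**2. The interferon count.** Let p_I and p_C be the true rates of a non-serious event on interferon and in controls, and a the share of interferon-arm events that unblinded investigators attribute to the drug.

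- Shown to the board: a × p_I on interferon, 0 in controls.
- What the board needs: p_I − p_C.

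The control rate p_C does not appear in what is shown, so the difference cannot be recovered from the summary.

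**3. Illustration (all rates assumed).** Take p_I = 20% and a = 0.5. Shown: 0.5 × 20% = 10% against 0%.

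| True control rate | True difference | Shown |
|---|---|---|
| 10% | 20 − 10 = +10 points | 10% v 0% |
| 20% | 20 − 20 = 0 points | 10% v 0% |

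**4. Illustration with the article's own interferon figures.** The article gives up to 80%, and says acetaminophen reduces the syndrome's symptoms by 80%. Reading that as a cut in incidence gives 80% × (1 − 0.80) = 16%. Assume control rates of 5% to 60%, full attribution (a = 1), and that these figures are the whole interferon-arm rate.

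| Interferon rate | True difference at control 5% | True difference at control 60% | Shown |
|---|---|---|---|
| 80% | 80 − 5 = +75 points | 80 − 60 = +20 points | 80% v 0% |
| 16% | 16 − 5 = +11 points | 16 − 60 = −44 points | 16% v 0% |

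The last assumption is crude, since treated participants also have background symptoms. The table shows only how wide a range of true differences fits one displayed result.

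**5. The recording exception.** Set the third exception beside the relatedness rule. A fever on the day after an injection can be entered as a drug-related event in the interferon arm. The same fever in a control, taken as COVID-19, is not entered as an adverse event at all. Lifting the filter alone would therefore still undercount controls for the symptoms that the drug and the disease share. The diary, kept in both arms, is the described source that does not depend on this attribution.

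**The case against.** The best case for the plan has four parts.

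- **The gap is confined.** Serious events as the protocol defines them, withdrawals and primary outcomes are not filtered on relatedness, and the board is said to review both groups. This stands and limits the point to non-serious events. It does not lift the filter, because the sentence that specifies the content applies it.
- **Attribution is not blind guesswork.** The article says the interferon syndrome falls within 4 to 24 hours of a dose and brings no respiratory symptoms or loss of smell. That helps with the expected syndrome. It does not help with an effect that nobody expects, and it supplies no control rate.
- **The board may see more than this.** The article is condensed, and fuller documents may provide further listings or let the board ask for them. That cannot be excluded. The rule criticised is nevertheless stated outright, and a board is less likely to ask about a signal that its standing report omits.
- **Enrolment was well advanced.** At submission, 251 of 310 households were enrolled. Monitoring continues until database lock, so cumulative tables would still be of use.

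A reader might infer more than the text supports. One inference is that the between-arm comparison is lost to the trial. It is not: recorded events in both arms, and the diaries, remain for the safety objective. Another is that an unfiltered adverse event record already holds everything needed, so that deleting a few words cures the fault. The third exception rules that out for flu-like symptoms. A third is that the board would be misled into taking 0% as a background rate. A board told that the column holds drug-related events would not read it so. The fault is missing information in one routine summary.

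**Conclusion.** The point holds for non-serious adverse events in the DSMB's per-meeting summary. The control count is zero by construction, the interferon count depends on unblinded attribution, and the two cannot be compared. The recording exception makes this worse for flu-like symptoms, where even an unfiltered event listing would undercount controls.

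This follows from the wording and needs no assumption about rates. Its practical size is unknown, because the documents give neither a control rate nor an attribution rate; every percentage in the two illustrations beyond the article's two 80% figures is assumed or derived from them. The change is worth making during the trial because it costs little, but it concerns reporting to the board and not the validity of the primary analyses.

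**What to change.** In the section on data and safety monitoring, replace the phrase that limits non-serious events to those thought drug-related with: *all recorded non-serious adverse events, by arm and participant type, regardless of relationship*. Show the investigator's attribution as an extra column. Participant type should separate index cases, treatment-eligible contacts and treatment-ineligible contacts, since the last group receives no study drug in either arm.

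Add a table of diary-recorded symptoms by arm, regardless of attribution, because the adverse event record alone undercounts symptoms shared by the drug and the disease. Diary reporting is itself open-label, so the table should be read with that in mind.

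The cost is a wording change, two tables from data already collected in both arms, and a longer DSMB report.

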### Primary and secondary objectives

The two co-primary objectives of this study are:To determine whether IFN ß-1a treatment reduces the proportion of infected cases shedding SARS-CoV-2 at day 11 after randomization.To determine whether IFN ß-1a treatment reduces the incidence of SARS-CoV-2 transmission from index cases to treatment-eligible household contacts, as measured by any positive upper airway infection evidenced by real-time Polymerase Chain Reaction (RT-PCR), in contacts at day 11 after randomization.

Secondary objectives of this study are:To determine whether in index cases infected with SARS-CoV-2, IFN ß-1a treatment compared with standard of care reduces the duration of SARS-CoV-2 upper airway virus shedding over 28 days following randomization.To determine whether IFN ß-1a treatment affects the incidence of SARS-CoV-2 upper airway infection or serological conversion by study day 29 in household contacts.To determine whether IFN ß-1a treatment compared with standard of care reduces the proportion of infected cases that require hospital admission or die due to COVID-19.To determine the safety of IFN ß-1a in the treatment and prevention of SARS-CoV-2 infection.

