Day 11	Brief physical examination Vital signs (forehead temperature, pulse, blood pressure, pulse oximetry) prior to study drug Review adverse events Review concomitant medications Collect completed diary cards and dispense new diary cards Saliva sample collection (immediately prior to study drug administration) Nasal lining fluid sampling for IgA Blood sample collection (2 tbsp; about 30 ml) Urine sample collection and pregnancy test pack, if applicable Administer acetaminophen 1000 mg PO pre-medication, if applicable Study drug administration, if applicable 12) Observation for 20 min post study drug administration, if applicable
Day 16 & 21 (± 24 h)	Diary completion Saliva sample collection
Day 29 (± 24 h)	Brief physical examination Vital signs (forehead temperature, pulse, blood pressure, pulse oximetry) Review adverse events Review concomitant medications Collect completed diary cards Blood sample collection Saliva sample collection Closure of study

Day 1 procedures must be executed within 72 h of a confirmed COVID-19 index case (RT-PCR evidence of SARS-CoV-2). During the first visit, participants will read and sign an informed consent form available as online appendices. Each household will also be randomized to IFN ß-1a treatment or standard of care. All study participants, regardless of their assignment, will be asked to monitor any symptoms of illness during the trial and, in particular, any ‘flu-like’ symptoms for the first 4–24 h following IFN ß-1a treatment, using an electronic diary. Study participants will be instructed to follow all recommendations from the Ministry of Health and advice from their medical providers in regard to COVID-19 clinical care. If participants are hospitalized during the study, all clinically relevant treatments will be provided as per health guidelines. Consent will be requested for access to medical records relating to any hospitalization or clinic visit.

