### Data analyses

Analyses of data for primary and secondary objectives will be conducted per protocol and through intent-to-treat using the procedures detailed below and described in greater detail in a statistical analysis plan, available upon request. Data analysts will be blind to treatment allocation. Analyses will be conducted using R and statistical coding will be available to the public upon request and approval by the investigators.

#### Analysis for primary objective 1

The Primary Objective 1 is to determine whether IFNß-1a treatment reduces the number of COVID-19 cases still shedding SARS-COV-2 in saliva at day 11 following randomization. Statistical analysis of SARS-CoV-2 RT-PCR results from the index case population will be undertaken comparing IFN ß-1a treated index cases to index cases receiving only standard of care. A linear regression model (binomial family, logit link for dichotomous outcomes) will be applied to data collected, where a risk ratio (and 95% confidence interval) will be reported for the treatment arm variable, adjusted for age, sex, baseline viral load and vaccination status at enrollment.

#### Analysis for primary objective 2

The Primary Objective 2 is to determine whether IFN ß-1a treatment reduces the incidence of SARS-CoV-2 transmission from an index case to treatment-eligible household contacts, as measured by upper airway RT-PCR in contacts at day 11 after randomization. Statistical analysis of SARS-CoV-2 RT-PCR results from household contacts will be undertaken comparing households assigned to IFN ß-1a treatment or standard of care. A linear regression model (binomial family, logit link for dichotomous outcomes) with clustering within a household will be applied, where a risk ratio (and 95% confidence interval) will be reported for the treatment arm variable, adjusted for age, sex, baseline viral load of the index case, vaccination status of the index case, vaccination status of eligible contacts, contacts between index case and household contacts during the initial 11-day period, baseline RT-PCR and antibody levels of treatment eligible contacts at enrollment, number of household members and physical details of the household size, e.g. number of bathrooms, number of bedrooms.

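### COVID-19 symptom onset in contacts is exempt from adverse event recording, but no stated outcome compares symptomatic illness short of admission between arms

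*Protocol article*

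**What the plan says.** The Data and safety monitoring section of the protocol article asks the investigator to record all adverse events whatever their relationship to treatment, with three exceptions. The third is "the onset of COVID-19 symptoms among asymptomatic household contacts", together with symptoms that newly appear in the index case. A separate rule on seriousness adds that "hospitalization due to progression of disease will not be considered a serious adverse event (SAE) for the purposes of this trial". Neither rule mentions an RT-PCR result.

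The Primary and secondary objectives section lists two co-primary and four secondary objectives. The co-primary for contacts is transmission, "as measured by any positive upper airway infection evidenced by real-time Polymerase Chain Reaction (RT-PCR), in contacts at day 11 after randomization". The secondary one is upper airway infection or seroconversion by day 29. A further secondary objective compares COVID-19 admission or death among infected cases. The safety objective covers interferon "in the treatment and prevention of SARS-CoV-2 infection".

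Under Baseline and follow-up home visits, symptoms are collected in both arms by electronic diary: "All study participants, regardless of their assignment, will be asked to monitor any symptoms of illness during the trial". The safety section says that interferon causes a flu-like syndrome in up to 80% of recipients, confined to 4 to 24 hours after a dose. It accepts that flu-like symptoms also occur in COVID-19, and states that "there are no respiratory symptoms or anosmia known to be associated with IFN use".

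**The concern.** Exempting the disease under study from adverse event recording is ordinary practice when the same event is counted as an outcome. Here the match is incomplete. The exemption removes symptom onset, while the outcomes stated for contacts count infection. Symptomatic illness that does not lead to admission falls between the two.

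Two consequences follow if the article is carried out as written.

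- Contacts in the interferon arm are without a known infection and receive a drug as prophylaxis. Suppose interferon lowered infection but left illness unchanged, or made infected contacts ill more often. The adverse event comparison would not show it. Nor would the summaries listed for the data and safety monitoring board, which are withdrawals, serious events, treatment-related non-serious events and primary outcome data.
- Because the exemption needs no RT-PCR result, staff who know the allocation could read fever or body aches after a dose as COVID-19 onset and leave them out of the adverse event record. That error can arise only where interferon is given, so it would understate reactogenicity in one arm.

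**Working it through.** **Stated outcomes against the exempted event.** The article gives no figure for symptomatic illness, so there is none to reproduce. The first check is a count over the six objectives.

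| Objective | Names contacts? | Captures symptomatic illness in contacts? |
|---|---|---|
| Co-primary 1: shedding at day 11 in infected cases | No; analysed in the index case population | No |
| Co-primary 2: RT-PCR at day 11 | Yes | No, infection only |
| Secondary: duration of shedding | No; worded for index cases | No |
| Secondary: infection or seroconversion by day 29 | Yes | No, infection only |
| Secondary: admission or death in infected cases | Not stated | Severe illness only, and only if the term includes contacts |
| Secondary: safety | Covers prevention | Symptom onset is exempted from adverse events |

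So 0 of 6 objectives name symptomatic illness in contacts, 2 of 6 name infection in contacts, and 1 of 6 may cover severe illness. The Data analyses section adds nothing: the contact analysis is of transmission "as measured by upper airway RT-PCR in contacts at day 11 after randomization", and secondary outcomes are to be analysed in the same way as the primary ones.

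**The term infected cases.** The shedding objective is limited to index cases in so many words, and the admission or death objective is not. That suggests the latter is broader. Yet co-primary 1 also speaks of infected cases and is analysed in index cases only. The text does not settle which meaning applies.

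**What a symptomatic outcome could detect.** Inputs from Sample size and power considerations: 278 evaluable households (139 per arm), 4 people per household, odds ratio 0.5, intra-class correlation 0.15. Assumptions: control risk of 10, 15 or 20% by day 29 (no rate is given), two-sided alpha 0.05, and m eligible contacts per household.

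The planned 417 contacts per arm are 139 × 3, that is, every household member other than the index case. They include enrolled treatment-ineligible contacts. Only one eligible contact per household is guaranteed, so m = 3 is the best case.

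- Contacts per arm n = 139m; design effect = 1 + (m − 1) × 0.15; effective n = n / design effect.
- Treated risk p2 = 0.5o / (1 + 0.5o), with o = p1 / (1 − p1). For p1 = 10, 15, 20%, p2 = 5.3, 8.1, 11.1%.
- Power = Φ(|p1 − p2| / SE − 1.96), with SE = √{[p1(1 − p1) + p2(1 − p2)] / effective n}.

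Example with m = 3 and p1 = 10%: effective n = 417 / 1.3 = 321; SE = √[(0.0900 + 0.0499) / 321] = 0.0209; 0.0474 / 0.0209 = 2.27; power = Φ(0.31) = 62%.

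| m | n per arm | Design effect | Effective n | Expected control events at 10/15/20% | Power at 10/15/20% |
|---|---|---|---|---|---|
| 1 | 139 | 1.00 | 139 | 14 / 21 / 28 | 32 / 44 / 54% |
| 2 | 278 | 1.15 | 242 | 28 / 42 / 56 | 50 / 66 / 78% |
| 3 | 417 | 1.30 | 321 | 42 / 63 / 83 | 62 / 78 / 88% |

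Leaving out contacts with symptoms on day 1 lowers every figure further.

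**The case against.** The strongest reply is that the trial's question for contacts is transmission, that infection is a legitimate endpoint for it, and that infection is counted twice. A contact with RT-PCR-confirmed illness by day 29 is an event in the day-29 outcome, and in co-primary 2 if positive at day 11. A reader might infer from the exemption that illness in contacts is never analysed, or that such events enter no analysis at all. The documents do not support that. The events enter as infections; what is missing is their comparison as illness.

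A reader might also say that the contact results rest on RT-PCR alone and so cannot tell prevented infection from a shorter positive period. That too goes further than the text, because the day-29 outcome includes seroconversion.

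The admission or death objective may cover infected contacts, so severe illness may be compared. The analysis plan and full protocol are not shown and may tabulate the diary data.

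These points narrow the concern but do not remove it. The objectives and the recording rule are stated in the article itself. A diary table elsewhere would neither make symptomatic illness a stated outcome nor tie the exemption to a positive RT-PCR.

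One further caution is fair. The article does not say which symptoms the diary itemises, so a definition based on respiratory symptoms or loss of smell depends on that.

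**Conclusion.** The point holds in limited form. Infection in contacts is analysed by arm. Symptomatic illness short of admission is exempted from adverse events, without an RT-PCR condition, and no stated objective or analysis takes it up. Whether severe illness in infected contacts is compared depends on an undefined term. The consequence is a blind spot in the safety comparison for prophylaxis and a route by which interferon reactions could go unrecorded; the infection analyses themselves are not affected.

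The reading that the 417 contacts per arm would give a well-powered symptomatic outcome is also not supported. The 62 to 88% range requires all three non-index members of each household to be treatment-eligible and symptom-free on day 1. With two it is 50 to 78%, and with one 32 to 54%. All of these rest on assumed control risks of 10 to 20% and the plan's odds ratio and intra-class correlation. The outcome would be supportive, not decisive. The change is worth making because it is cheap, and the conclusion about the gap does not depend on the power figures.

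**What to change.** 1. Add a secondary outcome: RT-PCR-confirmed symptomatic COVID-19 by day 29 in treatment-eligible contacts symptom-free on day 1. Compare it by randomised arm with the household-clustered model and report the estimate with its confidence interval.
2. For the main definition, count respiratory symptoms or loss of smell if the diary records them, since the article says interferon is not known to cause these. As a sensitivity analysis, count onset of any symptom outside the 24 hours after a dose, and exclude the same windows after the day 1, 6 and 11 visits in the control arm so that time at risk is equal.
3. For these contacts, apply the adverse event exemption only to RT-PCR-confirmed events counted in that outcome. Other symptom onsets stay in the adverse event record.
4. State whether infected cases in the admission or death objective include contacts who become infected.

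The cost is one outcome, one model and two sentences of definition. Diary data, and saliva from days 1, 6, 11, 16, 21 and 29, are already collected in both arms. The downside is self-reported symptoms in an open-label trial, which RT-PCR confirmation and the restricted symptom list reduce but do not remove. The narrower list also misses illness that shows only as fever, headache or body aches, which is why the sensitivity analysis is needed.
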